# Meta-analyses

Results from each embedded trial will ultimately be combined in meta-analyses. The BAMP sub-study will not be included in these meta-analyses due to its hypothetical nature. The meta-analyses will be displayed graphically using forest plots, which display the effect size estimates and confidence intervals for each trial in addition to the overall result.

## 8.1 Recruitment

Two random effects meta-analyses will be conducted using the odds ratio for each of the host trials which were calculated in the recruitment primary analysis (PIS only vs MMI only) and the recruitment secondary analysis (MMI & PIS vs PIS only). FORCE cannot be included in the second meta-analysis as only two arms (PIS only and MMI only) were used in the trial. The I2 statistic will be used to assess the heterogeneity between the trials. A sensitivity analysis for each meta-analysis will be carried out, in which a fixed-effects model will be used.

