# Sample Size

## 4.1 Overall

The sample size for each SWAT will ultimately be determined, and constrained, by the number of people approached to take part in the host trial.

An example sample size calculation based on the expected baseline recruitment rate of the host trials (that is, their recruitment rate without the intervention), is provided. A baseline recruitment rate of 20% to 80% is assumed, to account for the known variation in trial recruitment rates. Given this uncertainty, we estimated the sample size based on the relative effect of the MMI alone (when compared to PIS alone). Further, we assumed 80% power at standard 5% Type I error (α rate) to detect the specified effect and we have characterised the effect size as an odds ratio, which is more robust for sample size calculation.

Assuming the typical recruitment rate is 20%, an odds ratio of 1.2 would mean an increase in recruitment rate using the MMI to 23.1%. To detect this in a single randomised controlled trial (with 1:1 randomisation between MMI and printed material arms), a sample size of 701 would be needed. If the typical recruitment rate is 80%, an odds ratio of 1.2 corresponds to an increase in recruitment rate to 82.8% and would require a sample size of 783.

Results from each embedded trial will ultimately be combined in a meta-analysis. Given that there will be different trials with variation in interventions, participants and baseline recruitment rates, it is plausible that the effectiveness of the MMIs at improving recruitment will vary; i.e. there will be heterogeneity in the observed odds ratios across trials. Adjusting for this is approximate (particularly as the heterogeneity is currently unknown), however, as a rough rule of thumb if the I2 statistic in the meta-analysis is 50% the sample size will double (1).

Given the three arm randomisation (with two of the arms being compared for the primary analysis), an additional 50% of people will need to be approached (i.e. 783 x 1.5 = 1,175). Furthermore, the adjustment for heterogeneity in effects of the MMI intervention across the six trials (estimated I-square value = 50%) means that the sample size should be doubled (i.e. 1,175 x 2 = 2,350).

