# Analysis

A CONSORT diagram displaying the flow of participants through each trial will be reported.

All analyses will be conducted in STATA v16 (StataCorp, [name]), or later (to be confirmed in final report), following the principles of intention-to-treat with participant’s outcomes analysed according to their original, randomised group. The following sections relate to the separate analyses of the host trials. Details of the meta-analyses are given in Section 8. Analysis of the primary outcome will be checked by a second statistician after they are conducted. The data relating to the main BAMP study and the BAMP sub-study will be analysed separately. Appropriate model diagnostics will be assessed when models are fitted, including checking normality (for continuous outcomes), checking normality of random effects and checking the homoscedasticity of residuals.

As all the analyses include the PIS only arm, it is important to consider the effect of this on the Type 1 error rate. Here, we will not adjust for multiplicity as we only have a single primary outcome comparison (rather than a co-primary outcome or a primary outcome that is a combination of the multiple comparisons).

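### Six very unequal host trials (five without FORCE) are pooled by random effects with no interval method suited to few trials, and the only sensitivity analysis cannot show the resulting under-coverage

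*SAP*

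**What the plan says.** Section 8.1 of the SAP specifies the pooling in one sentence: "Two random effects meta-analyses will be conducted using the odds ratio for each of the host trials". I-squared is to describe heterogeneity, and there is one robustness check: "A sensitivity analysis for each meta-analysis will be carried out, in which a fixed-effects model will be used". Sections 8.2 and 8.3 follow the same pattern for retention and decision quality. None of them names an estimator of the between-trial variance, an interval type or a small-number correction.

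Six trials enter the MMI-only versus PIS-only contrast. The second contrast has five: "FORCE cannot be included in the second meta-analysis as only two arms (PIS only and MMI only) were used in the trial". Table 1 gives expected TRECA sizes of 1071 (FORCE, cluster randomised, two arms), 413 (CHAMP-UK), 118 (THERMIC-3), 100 (BALANCE), 50 (UKALL) and 10 (BAMP).

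Section 4.1 plans for heterogeneity. It adopts I-squared of 50% and reasons that "as a rough rule of thumb if the I2 statistic in the meta-analysis is 50% the sample size will double". Its target effect is an odds ratio of 1.2, for which "we assumed 80% power at standard 5% Type I error (α rate) to detect the specified effect".

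The primary outcome (Section 6.1) and primary analysis (Section 7.2) are written trial by trial, while the sample size in Section 4.1 is built for the combined analysis. No sentence labels the pooled odds ratio as the primary result.

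**The concern.** With five or six trials the between-trial variance is poorly estimated. The usual random-effects interval, estimate ± 1.96 standard errors, treats that variance as known. When heterogeneity is real and one trial dominates, the interval is too short. The SAP expects heterogeneity, and its own Table 1 shows the dominance.

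At stake is the pooled MMI-only versus PIS-only odds ratio, which Section 4.1 relies on to evaluate the MMIs robustly. A 95% interval that covers clearly less than 95% overstates the evidence in either direction. The fixed-effects check assumes no heterogeneity at all, so agreement between the two models would be false reassurance. If the interval method stays open, it will be chosen after the data are seen.

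**Working it through.** **The plan's own figure.** The SAP states no coverage figure. Its later sample-size steps are arithmetically right (783 × 1.5 ≈ 1,175; × 2 = 2,350; ÷ 6 ≈ 392). The starting values of 701 and 783 were not reproduced by the standard two-proportion formula. That is a separate matter and nothing below uses them; only I-squared 50% and the odds ratio of 1.2 are carried forward.

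**Inputs.** Sizes are from Table 1. Section 5 gives 1:1:1 allocation outside FORCE, so each arm has one third of a three-arm trial and one half of FORCE. Baseline rates are 20%, 50%, 80% or mixed, within the 20–80% of Section 4.1. No intracluster correlation is given for FORCE, so design effects D of 1, 2 and 4 are assumed.

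**Step 1: weights.** For trial i with n per arm, v = 1/[n·p0(1−p0)] + 1/[n·p1(1−p1)], multiplied by D for FORCE. At p0 = 0.50, an odds ratio of 1.2 gives p1 = 1.2/2.2 = 0.545. With D = 1:

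| Trial | n per arm | v | weight 1/v |
|---|---|---|---|
| FORCE | 535.5 | 0.0150 | 66.7 |
| CHAMP-UK | 137.7 | 0.0583 | 17.1 |
| THERMIC-3 | 39.3 | 0.204 | 4.9 |
| BALANCE | 33.3 | 0.241 | 4.1 |
| UKALL | 16.7 | 0.482 | 2.1 |
| BAMP | 3.3 | 2.41 | 0.4 |

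The weights sum to 95.3. FORCE carries 66.7/95.3 = 70% of the fixed-effect weight and BAMP 0.4%.

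**Step 2: heterogeneity.** Two readings of 50% were used.
- Literal I-squared: I² = τ²/(τ² + s²), with typical variance s² = (k−1)Σw/[(Σw)² − Σw²]. I² = 50% means τ² = s². In the example, s² ≈ 5 × 95.3/(9,087 − 4,783) ≈ 0.111, so τ ≈ 0.33.
- Variance doubling, as in Section 4.1: τ² solves 1/Σ[1/(v+τ²)] = 2/Σw, giving τ² ≈ 0.025 (τ ≈ 0.16) in the example.

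**Step 3: coverage of a nominal 95% interval at literal I² = 50%.** There were 40,000 runs under the normal model, and 20,000 binomial runs with 0.5 added for empty cells. The normal interval was computed with DerSimonian-Laird and with REML. The floored Hartung-Knapp interval does not let its standard error fall below the conventional one.

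| Setting | Normal interval | Plain Hartung-Knapp | Floored Hartung-Knapp | Fixed effect |
|---|---|---|---|---|
| Six trials, D = 1 | 82.5–84% | 86–88% | 90–92% | 55–57% |
| Six trials, D = 2 | 86–87.5% | 89–91% | 93–94% | 68–69% |
| Six trials, D = 4 | 88–89% | about 92% | 95% | 73% |
| Five trials | 87–88% | 90–91.5% | 95–96% | 68–72% |

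A separate 40,000-run check of the normal interval gave 83%, 87%, 87% and 88% at D = 1 to 4, and 87% for five trials. Another run put fixed-effect coverage as low as 53% for six trials.

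**Step 4: other settings.** Under the variance-doubling reading, the normal interval covers 89–91% (six trials) and 90–90.5% (five). With no heterogeneity it covers 96–97%. Leaving out BAMP changes little: 83–85% with FORCE, 88–89% without. Six equal trials at I² = 50% would give about 92%, so imbalance adds to the small number of trials.

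**Step 5: widths.** At a 50% baseline with D = 1, mean log-odds interval width is 2 × 1.96/√95.3 = 0.40 for fixed effects against 0.75 for DerSimonian-Laird. For the same variance estimate, the floored interval must be at least 2.571/1.96 = 1.31 times as wide as the normal one with six trials (5 df), and 2.776/1.96 = 1.42 times with five (4 df). In simulation at τ = 0.4 the median half-widths for six trials were 0.58 and 0.43, a ratio of 1.35. For five trials the ratio is about 1.45.

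**The case against.** The SAP says only random effects, so an analyst following it could already use a Hartung-Knapp interval. That stands: the 83–88% describes the conventional choice, not a stated one, and the defect is that the choice is left open.

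The literal reading of I-squared implies large heterogeneity. With τ = 0.4, trial odds ratios would run from about 1.2·exp(−0.784) = 0.55 to 1.2·exp(0.784) = 2.63, and τ itself is more than twice the planned effect (log 1.2 = 0.18). Under the milder reading the shortfall roughly halves, and with no heterogeneity it disappears. The lowest figures also assume no clustering loss in FORCE. All of this stands and makes the size conditional, but every heterogeneous setting examined falls short of 95%.

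The remedy is a trade-off. It does not reliably restore 95% for six trials, it widens an interval that is already wide relative to 0.18, and it covers about 99% if there is no heterogeneity. Retention and decision scores were not simulated.

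Three stronger readings are tempting and not supported.
- A reader might infer a false-positive rate of 12–17% outright. That requires both the normal interval and the literal I-squared.
- A reader might infer that the fixed-effects interval is always narrower. It coincides with the DerSimonian-Laird interval when heterogeneity is estimated as zero, in about 25–30% of runs at I² = 50%.
- A reader might set Section 7's "we only have a single primary outcome comparison" against a p-value in each of six trials and compute 1 − 0.95⁶ = 26%. That sentence concerns the two contrasts sharing the PIS-only arm. BAMP, with about three per arm, can hardly reject, and nowhere does the SAP let one host trial's p-value settle the question.

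**Conclusion.** The point holds in conditional form and is worth correcting before analysis. For recruitment, if the conventional normal interval is used at I-squared 50%, nominal 95% intervals cover about 83–88% with six trials and about 87% with five. This rests on the Table 1 sizes, an assumed FORCE design effect of 1 to 4 and the literal reading of I-squared. If 50% means only the doubling in Section 4.1, coverage is about 89–91%; with no heterogeneity, about 97%. The planned fixed-effects check covers roughly 53–73% at I-squared 50% and is never wider than the main interval, so it cannot expose the weakness. The documents do not establish a multiplicity error here. They do leave unsaid that the pooled odds ratio is the primary result.

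**What to change.** - In Section 8.1, specify REML with a Hartung-Knapp t-based interval on k − 1 degrees of freedom, with the standard error not allowed below the conventional one. Use it as the main interval, or at least as a sensitivity analysis beside the fixed-effects model. The plain version is not enough with sizes this unequal.
- Apply the same wording in Sections 8.2 and 8.3 for consistency.
- State in Section 8.1 that the pooled MMI-only versus PIS-only recruitment odds ratio is the primary result.

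Expected coverage at I-squared 50% becomes about 91–95% for six trials, which is better but not fully restored, and about 95% for five. The change is a wording amendment and needs no new data. The price is the wider intervals shown in Step 5 and some conservatism if the host trials prove homogeneous.

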## 8.2 Retention

Two random effects meta-analyses will be conducted using the odds ratio for each of the host trials which were calculated in the retention secondary analyses. The I^2^ statistic will be used to assess the heterogeneity between the trials. A sensitivity analysis for each meta-analysis will be carried out, in which a fixed-effects model will be used.

## 8.3 Quality of decision making

The decision making data from all six trials (including the BAMP main trial, but not the BAMP sub-study) will also be combined in four meta-analyses, which will mirror the four analyses specified in section 7.3.2. Mean difference scores from each of the trials will be combined in a random effects meta-analysis. A sensitivity analysis for each meta-analysis will be carried out, in which a fixed-effects model will be used.

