### 6.2.3 Quality of Decision Making

We will also measure the quality of decision making by potential host trial participants. Children and adolescents will be asked to complete a brief decisional scale, adapted from one used within the REFORM trial (unpublished data; [name], [name], [name], [name], [name]) and drawing conceptually on the SURE (3, 4) and DelibeRATE scales (5). When a parent/carer has been involved in the participation decision, we will also ask them to complete the scale. The scale has been adapted to facilitate completion by young children. We will aim to obtain decision quality scores both from individuals who decide to participate in the host trial and those who decline.

In patients who decide to take part, the children and adolescents and/or parent/carer will be asked to complete the decisional scale once the host trial participation documentation has been completed. In patients who decline participation, they will be asked to complete this measure in the clinic or will have them posted at home or emailed, as appropriate.

The adolescent and parent/family versions of the questionnaire contain the same number of questions, with slight changes in the phrasing of questions. The decisional scale contains 9 Likert questions (with 5 possible answer options) and there are a further 3 questions containing space for free text which give participants the opportunity to give further opinion on their experience. There is also a question detailing who filled in the questionnaire (‘patient’ or ‘parent/carer and patient together’). The younger patient version of the questionnaire is of a similar format. The decisional scale contains 3 Likert questions (each with 5 possible answer options) and the further 3 open ended questions (Please see appendix).

The decisional scales will be scored for both the 3 and 9 question version. Answers to each Likert question will be allocated a value of 0-4. The values for each question will be summed to create an overall score, out of 12 and 36, for the two versions of the scale. Up to three missing responses will be allowed on the 9 question scale. One missing value will be allowed on the 3 question version of the scale. A total score will be calculated by replacing the missing values with the mean score from the completed responses given by the participant. Any scores with more than 3 (adolescent and parent/family version) or more than 1 (younger patient version) will not be scored.

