### 7.3.3 Quality of Decision Making

The responses to each question (including the amount of missing responses) and the calculated total scores of the decisional questionnaire will be summarised descriptively overall and broken down by host trial, TRECA allocation and type of questionnaire (younger patient, adolescent or parent/family). A bar chart showing the total scores for each of the three TRECA arms will be included.

As a patient and their parent/carer may both fill in a questionnaire, all the data from the all three questionnaires will not be combined, as all the scores would not be independent. Hence, scores for patients (younger or older) and parents/family questionnaires will be analysed separately using a linear regression, with TRECA allocation and host trial status (whether the participant went on to enter the trial) included as a covariates. Clustering will be accounted for by using the cluster variable as a random effect. Mean difference will be presented with 95% confidence intervals.

If both the younger and older patient questionnaires are used in a host trial the questionnaire data from the younger and older patient questionnaires will be combined. The scores for these will be standardised within the trial by subtracting the sample mean score from the observed score and dividing the result by the sample standard deviation, where the ‘sample’ refers to the subset of participants that have used that questionnaire. Then the standard scores for all participants will be analysed as described above.

To assess the robustness of the method used to replace the missing values, a sensitivity analysis will be conducted, where the analysis will be repeated using only the questionnaires in which all 9 questions were answered.

Both the above analyses (in this section) will be repeated for only the participants who went onto to enter a trial.

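### The patient-score meta-analyses in SAP section 8.3 pool mean differences in three units, so the pooled size, unit and weights cannot be interpreted

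*SAP*

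**What the plan says.** **Scoring.** Section 6.2.3 gives two lengths of form. For the younger version, "The decisional scale contains 3 Likert questions (each with 5 possible answer options"; the adolescent and parent/family versions have nine such questions. "Answers to each Likert question will be allocated a value of 0-4", and the item values are "summed to create an overall score, out of 12 and 36, for the two versions of the scale".

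**Within-trial analysis.** Section 7.3.3 analyses patient scores and parent/family scores separately by linear regression and reports mean differences. Standardising is conditional: "If both the younger and older patient questionnaires are used in a host trial", scores are centred and divided by the sample SD of those who used that version. Nothing is said about standardising in a trial with one patient version. The sensitivity analysis for missing items is run "using only the questionnaires in which all 9 questions were answered".

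**Pooling.** Section 8.3 says the data will be "combined in four meta-analyses, which will mirror the four analyses specified in section 7.3.2". Section 7.3.2 is Retention, so section 7.3.3 must be meant. The effect measure is set by one sentence: "Mean difference scores from each of the trials will be combined in a random effects meta-analysis". No standardised mean difference, rescaling or split by version is named.

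**Forms by trial.** Table 1 lists the younger form alone for BALANCE and CHAMP-UK patients, the older form alone for BAMP, both for THERMIC-3 and UKALL, and no patient form for FORCE. All six trials use the parent/family form.

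**The concern.** Within a trial, the plan recognises that a 12-point and a 36-point total cannot be mixed raw, and it standardises them. It does not carry that step across trials, where the same two totals meet again alongside the standardised scores.

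An inverse-variance meta-analysis assumes that every input estimates an effect in the same unit. When units differ, the trial whose unit gives the smallest numerical variance gains weight for that reason alone, and the pooled number belongs to no scale. Effects that are equal in SD terms also enter as different numbers, which can look like heterogeneity. The planned fixed-effects sensitivity analysis uses the same inputs, so it cannot reveal the problem. Decision quality is among the stated aims in section 3 of the SAP, so a pooled patient result is likely to be reported and read.

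**Working it through.** **1. The plan's own figures.** Younger form: 3 × 4 = 12. Older and parent/family forms: 9 × 4 = 36. SD on 0-36 in section 4.2: (31.5 − 4.5)/4 = 6.75. All reproduce.

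**2. Unit of each trial's patient mean difference** (Table 1 with section 7.3.3)

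| Trial | Expected TRECA N | Patient form | Unit |
|---|---|---|---|
| BALANCE | 100 | younger | 0-12 points |
| CHAMP-UK | 413 | younger | 0-12 points |
| BAMP | 10 | older | 0-36 points |
| THERMIC-3 | 118 | both | SD |
| UKALL | 50 | both | SD |
| FORCE | 1071 | none | no patient score |

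The five trials with patient scores expect 100 + 413 + 10 + 118 + 50 = 691 participants.

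**3. Weights (illustration).** Assumptions: SD 6.75 on 0-36 (stated for the BAMP sub-study); SD 2.25 on 0-12 (assumed in proportion, 6.75 × 12/36); SD 1 for standardised scores; arms of N/3; the same response rate in every trial.

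Variance of a mean difference = 2 × SD²/n per arm, so the fixed-effect weight is proportional to N/SD²:

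- BALANCE: 100/5.0625 = 19.75 (7.3%)
- CHAMP-UK: 413/5.0625 = 81.58 (30.3%)
- BAMP: 10/45.5625 = 0.22 (0.1%)
- THERMIC-3: 118/1 = 118 (43.8%)
- UKALL: 50/1 = 50 (18.5%)
- Sum: 269.55

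THERMIC-3 plus UKALL: 168/269.55 = 62% of the weight with 168/691 = 24% of participants. CHAMP-UK: 30% of the weight with 413/691 = 60% of participants. On a common SD scale the weights simply follow N.

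**4. Varying the assumed SD on 0-12.**

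- SD 1.5: 168/(44.44 + 183.56 + 0.22 + 168) = 168/396.22 = 42%
- SD 3.0: 168/(11.11 + 45.89 + 0.22 + 168) = 168/225.22 = 75%

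**5. Varying response.** If 20% respond in THERMIC-3 and UKALL and 60% elsewhere, their term falls to 168/3 = 56. The share is then 56/(19.75 + 81.58 + 0.22 + 56) = 56/157.55 = 36%, and CHAMP-UK has 81.58/157.55 = 52%. In that case the two trials supply 33.6 of 347.4 forms, about 10%.

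**6. Pooled value for one identical effect.** A true effect of 0.3 SD everywhere enters as 0.3 × 2.25 = 0.675, 0.3 × 6.75 = 2.025 and 0.30.

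Pooled: (19.75 × 0.675 + 81.58 × 0.675 + 0.22 × 2.025 + 168 × 0.30)/269.55 = 0.44, which is neither points nor SDs. On a common scale it is 0.30 SD.

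**7. Test of no effect.** At 60% response, n per arm = 0.2N, so the total weight is 0.1 × ΣN/SD².

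- As written: SE = 1/√26.955 = 0.193, z = 0.442/0.193 = 2.30 before rounding.
- Common scale: SE = 1/√69.1 = 0.120, z = 0.3/0.120 = 2.49 before rounding.

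**8. Heterogeneity from the units alone.** With 0.3 SD and 60% response, Q = 0.94 on 4 df, so I² = 0%. With 0.667 SD (4.5/6.75, the difference called meaningful in section 4.2), I² is about 48% at full response, 14% at 60% and 0% at 50%. On a common scale it is 0% throughout.

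**9. Sensitivity rule.** A 3-question form can never have nine questions answered. Read literally, the rule leaves no patient data in BALANCE and CHAMP-UK and only older-form patients in THERMIC-3 and UKALL, although section 6.2.3 allows one missing item on the younger form.

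**The case against.** The other side has several sound points.

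- **The result is not empty.** The answer options in the example forms run from less to more favourable on both versions, and zero means no difference in every unit. Sign and test survive (z 2.30 against 2.49), and the forest plots in section 8 show each trial separately. A reader might infer that the pooled estimate has no meaning at all; that goes too far.
- **Spurious heterogeneity is not certain.** A reader might infer that the units must inflate I². Step 8 shows that this depends on the effect size and response, and section 8.3, unlike 8.1 and 8.2, does not name I².
- **The weights are assumption-driven.** The SD on 0-12 is not in the SAP, and Table 1 counts people approached, not completed forms. The example forms cover ages 5-11 and 12-18, so younger children may have none. Step 5 shows the share falling to 36%. It still far exceeds those trials' share of forms in that scenario.
- **The reference to six trials is not an error.** A reader might infer that FORCE is wrongly placed in the patient analysis. Section 8.3 speaks of the whole set of meta-analyses, and FORCE supplies parent/family scores.
- **The nine-question rule may be a slip.** Its purpose covers both forms, so loose wording is the likelier explanation. It is a separate matter from pooling.

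None of this supplies a common unit. Nothing elsewhere in the SAP does so.

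**Conclusion.** The point holds for the patient-score meta-analyses, including the repeat limited to those who entered a host trial. Followed as written, section 8.3 gives a pooled patient effect in no identifiable unit, with weights set partly by the choice of unit. That there are three units follows from the SAP alone. The size of the distortion is illustrative: about 62% of the fixed-effect weight on two trials with 24% of expected participants, or 42% to 75% over 0-12 SDs of 1.5 to 3.0, given equal response. Random-effects weights would also depend on the between-trial variance, which the mixed units can themselves affect.

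The parent/family meta-analyses and the primary outcome are untouched. Because only a secondary outcome is affected and its direction stays readable, this should be fixed but does not undermine the main result.

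**What to change.** In section 8.3, state that patient scores are standardised within questionnaire version in every host trial, including those with one version, or that standardised mean differences are pooled. Give the unit as SDs, and note that five trials contribute patient scores. Keep raw points for the parent/family meta-analyses. Correct the cross-reference to section 7.3.3 at the same time.

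Separately, in section 7.3.3, reword the complete-form rule to require all 9 questions answered or, for the younger version, all 3.

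The cost is a few lines of text and one extra transformation of data already collected. Making the change before the results are seen avoids a post hoc choice of scale.
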